### 2.3. Sample Size and Procedure

We estimate that the difference between the two percentages of subjects in terms of iodine uptake at the end of treatment will equal 30% (for example, 60% in the experimental group and 30% in the control group). We also set the alpha error and power at 5% and 80%, respectively. Given these conditions, 42 patients per group will be necessary for the effect size indicated above to lead to a statistically significant result. A total of 84 patients will therefore need to be enrolled. A chi-square test will be used for the primary endpoint. Univariate and multivariate tests will be used for secondary endpoints. A multivariate logistic regression will be performed adjusting for gender and age.

The patients will be enrolled with a 1:1 ratio in either the control (KI group) or treatment MI (KI plus MI group) groups. The randomization list will be generated using Excel. We will include RAIR-TC patients being treated with KIs as per clinical practice. The enrolled patients will be divided into groups based on the KI type and then into two subgroups: KIs only vs. KIs plus MI. All patients will need to give their written informed consent to be included in the study. If not already available for all patients, an NGS molecular panel will be performed to look for somatic mutations. Each patient will be identified by a two-digit code and patient initials, which are the only identification elements and will only be used for the purposes of the study. Clinical data will be collected during the randomization, on the first (Day 1) and last day (Day 30) of the supplementation with MI (in both the KI and KI plus MI groups), and then on the day of the whole-body scintigraphy (Day 35).

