The first clinical phase II study to test the mKI sorafenib reported that, of the 20 patients evaluated for re-differentiation, only one showed a weak restored uptake of RAI in an occipital skeletal metastasis on a diagnostic whole-body scan (WBS); however, this was not confirmed on the therapeutic WBS [14]. Renewed interest in the re-differentiation strategy arose after a study by the James Fagin laboratory (Memorial Sloan-Kettering Cancer Center) [15]. In this latter study, an ingenious mouse model expressed the BRAFV600E oncogene in thyrocytes, and the expression of the BRAFV600E could be switched on or off with the administration or withdrawal of doxycycline. A MEK inhibitor (selumetinib) or BRAFV600E inhibitor (dabrafenib) partially restored thyroid-specific gene expression and RAI uptake. Following this preclinical in vivo study, a pioneer study by the Memorial Sloan-Kettering Cancer Center by Ho et al. in 24 patients with PTC or follicular-TC (FTC) or PDTC confirmed the ability of selumetinib to restore RAI uptake in 44% of the BRAFV600E-mutated DTC patients, who were then treated with 131I, resulting in partial tumor responses in 11% of these patients [16].

More recently, a considerable number of preclinical studies have confirmed that inhibiting the MAP kinase pathway can induce re-differentiation and tumor responses in BRAFV600E-mutated TC with clinical benefits [17,18,19,20,21]. Overall, these studies show that cellular de-differentiation may be reversible in terms of both the re-uptake of iodine and the synthesis of specific proteins such as thyroglobulin. However, during treatment, on-target and off-target mutations may be a potential general mechanism of resistance. Most in vitro and in vivo studies have used sKIs; however, some studies have also shown that cabozantinib and lenvatinib increased RAI uptake [13,22,23]. This is not surprising considering that, although mKIs have multiple targets, and although the main effect of lenvatinib is on vascular endothelial growth factor receptor (VEGFR) 1–3, this drug also interacts with platelet-derived growth factor receptor (PDGFR) and the PI3K/Akt pathway.

The literature data also suggest that myo-inositol (MI) may play a role in potentiating the action of KIs at various levels.

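### Patients are allocated within kinase-inhibitor (KI) type, but neither the primary chi-square nor the logistic model includes it; if uptake differs clearly by KI type, the test is conservative and less efficient

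*Protocol article*

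**What the plan says.** All of this is in section 2.3 of the protocol article unless noted.

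- **Allocation:** "The enrolled patients will be divided into groups based on the KI type and then into two subgroups: KIs only vs. KIs plus MI". The ratio is 1:1 and the list is made in Excel. The word stratified is not used and no block method is given.
- **Size:** "We also set the alpha error and power at 5% and 80%, respectively", with rates given as "for example, 60% in the experimental group and 30% in the control group", so that "42 patients per group will be necessary for the effect size indicated above to lead to a statistically significant result". No rates by KI type are given.
- **Primary test:** "A chi-square test will be used for the primary endpoint".
- **Adjusted model:** "A multivariate logistic regression will be performed adjusting for gender and age". This follows the sentence on secondary endpoints, so its link to the primary endpoint is not clear.
- **Level of comparison:** section 2.2 says that comparisons will be between the same KI subgroups of the two arms. The sizing in 2.3 is for a single overall comparison.
- **Background rates:** the Introduction reports that a selective inhibitor could "restore RAI uptake in 44% of the BRAFV600E-mutated DTC patients", and that with a multikinase inhibitor, "of the 20 patients evaluated for re-differentiation, only one showed a weak restored uptake of RAI".

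**The concern.** KI type follows from genotype: dabrafenib plus trametinib for BRAF-mutated disease, lenvatinib otherwise. The Introduction gives some reason to expect iodine uptake to differ between the two. It gives none for gender or age, which are the two covariates chosen.

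When arms are balanced within strata that have different response rates, the difference between strata cannot contribute to the difference between arms. A chi-square on the collapsed 2x2 table still counts it as noise. The variance is then too large, p-values are too big, and part of the precision gained from allocating by KI type is lost.

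The text also leaves open what the primary comparison is. Section 2.3 implies one overall test, while section 2.2 implies comparison within KI type.

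**Working it through.** **1. The plan's own figure.** Two-sided alpha 5% (sidedness is not stated, but this reproduces the number), power 80%, rates 60% and 30%, mean 45%:

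n = [1.960·√(2·0.45·0.55) + 0.842·√(0.60·0.40 + 0.30·0.70)]² / 0.30² = 41.97, so 42 per group. This agrees with the plan.

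**2. Why the collapsed test is conservative.** Assume equal strata, 1:1 balance in each, and no MI effect. The true variance of the difference is proportional to the mean of p(1−p) over the strata. The collapsed chi-square uses p̄(1−p̄). At 44% and 5%:

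- True: (0.44·0.56 + 0.05·0.95)/2 = 0.1470
- Used: 0.245·0.755 = 0.1850
- Ratio 0.794, square root 0.891. The effective critical value is 1.96/0.891 = 2.20, which gives a two-sided size of about 2.8%.

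With a 30-point effect (74% and 35% on MI), the standard error is 0.1015 collapsed and 0.0922 stratified, a variance ratio of 1.21.

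**3. Exact results.** These come from full enumeration of four binomials with 21 per cell, comparing the collapsed Pearson chi-square with the CMH test without continuity correction. The 21-per-cell split and all rates by KI type are assumptions. Each cell shows chi-square / CMH.

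| Control rates by KI type | Size | Power, +20 points | Power, +30 points |
|---|---|---|---|
| 44%, 5% | 2.9% / 5.2% | 49.7% / 57.1% | 85.6% / 88.8% |
| 50%, 10% | 3.0% / 5.1% | 49.2% / 54.1% | 85.1% / 87.6% |
| 40%, 20% | 4.5% / 5.0% | 49.4% / 49.2% | 83.3% / 82.6% |
| 30%, 30% | 5.1% / 5.1% | 49.4% / 47.6% | 82.8% / 79.7% |

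At 44% and 5% with 14 and 28, or 28 and 14, patients per arm in the two KI types, the chi-square's size is 2.8% and 3.3%; CMH gives 5.1% and 5.0%.

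If MI acts through a common odds ratio of 3.5 (the odds ratio of 60% vs 30%: 1.5/0.4286), power in equal strata is 49.4% / 62.1% at 44% and 5%, and 61.5% / 68.2% at 50% and 10%.

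**4. If balance is not forced.** With coin-toss allocation inside each KI type (simulation, 42 patients per KI type), the chi-square's size at 44% and 5% is 5.0%. Its power at +30 points is 81.2%, against 88.0% for CMH. The conservatism disappears but the efficiency gap remains.

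**5. If section 2.2 means separate tests.** Power for 60% vs 30% within one KI type is about 50% with 21 per arm, 35% with 14 and 62% with 28.

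**The case against.** The strongest case against has five parts.

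- **Section 2.2 may already deal with KI type.** If comparisons are run within each KI type, nothing is collapsed. This stands as a reading, but it conflicts with the 42 vs 42 sizing and would leave each test at about 50% power with 21 per arm. It moves the problem rather than removing it.
- **The effect is conditional.** A reader might infer that the test's error rate is wrong as it stands. The documents do not support that. The size leaves 5% through KI type only if allocation is balanced within type, which the article describes but does not secure with a stated method, and only if uptake differs clearly. At 40% and 20% the size is 4.5%.
- **Direction.** A reader might also fear false positives. Any departure due to KI type is below 5%. The chi-square's exact size does reach 6.2% when both types share a 45% rate, but that is discreteness of the table at 42 per arm and has nothing to do with KI type.
- **Planned power is not lost.** At a 30-point effect with balance, the chi-square has 83% to 86% power in the tabulated cases. It is slightly ahead of CMH when the rates are equal or 20 points apart. This stands.
- **The 44% and 5% figures are weak inputs.** They come from selumetinib and sorafenib, neither a trial drug. The Introduction also says that lenvatinib has raised uptake in some studies. This stands, so the rates serve only as an illustration.

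A separate analysis plan might add KI type. The article nevertheless names both the test and the covariates, and the factor used for allocation is in neither.

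**Conclusion.** The mismatch between allocation and stated analysis is in the text and holds. Its consequence is limited and conditional. With balance within KI type and a wide difference in uptake (44% vs 5%, or 50% vs 10%), the collapsed test works at about 3% instead of 5%. It gives up about 5 to 7 points of power at a 20-point effect and 2.5 to 3 points at a 30-point effect. The loss is larger under a common odds ratio, at 7 to 13 points in equal strata. With a 20-point difference between KI types there is almost nothing to gain, and with none the chi-square is ahead by about 3 points at the design effect.

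This is a matter of efficiency and of matching analysis to design, and it does not threaten the validity of a positive result. All figures rest on assumed stratum sizes and assumed rates by KI type, since the article gives neither. The change is worth making because it is nearly free and also settles the conflict between sections 2.2 and 2.3.

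**What to change.** In section 2.3 (and the analysis plan, if there is one), before outcome data are seen:

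1. Make the primary test a single CMH test stratified by KI type, without continuity correction, on all 84 patients.
2. Report the Mantel-Haenszel risk difference stratified by KI type, with its 95% CI.
3. Add KI type to the logistic model beside age and gender, and say whether that model applies to the primary endpoint.
4. State that this one test is the primary comparison. It compares like with like within KI type, as section 2.2 asks, and keeps the overall sizing of section 2.3.

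The cost is a few sentences. KI type is known at allocation, so no new data are needed, and the sample size need not change. The downside is power of about 79.7% instead of 82.8% at 60% vs 30% if uptake does not depend on KI type, which is marginally under the stated 80%.

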In the protocol, we need to tackle the issues regarding the dose of MI and the time of administration. MI has a half-life of about 24 h and may thus reach a steady state after 4–5 days. However, we preferred a more prolonged administration period to enable the optimal incorporation of MI in the plasma membrane. Another important aspect concerns the dosage. According to the literature, a 4 g dose of MI shows significant clinical efficacy across different pathological conditions [35,36]. This is also the maximum dose allowed by the Italian Ministry of Health for use as a nutraceutical (https://www.salute.gov.it/new/sites/default/files/imported/C_17_pagineAree_1268_4_file.pdf Accessed on 21 December 2025). It is worth noting, however, that several studies have also demonstrated the effectiveness of MI at lower doses, particularly in the management of thyroid disorders [37,38,39].

In the present study, we will include α-lactalbumin in the supplement alongside MI, because this prebiotic molecule plays an important role in enhancing the intestinal absorption of MI through the gap junctions of enterocytes [40].

In addition to adding MI to the KI treatment, which is the main aim of our investigation, our protocol has several differences compared to previous protocols for the re-differentiation of TC by KIs.

In most protocols, KIs were administered for re-differentiation purposes only when the tumor was in progression, and RAI uptake was investigated shortly afterwards. For this reason, in some cases, the final clinical effects (KI itself vs. RAI therapy) on tumor mass and progression were not clearly separable.

In our protocol, patients have already been on treatment with KIs for a reasonably long time, and thus, any subsequent clinical effect of RAI therapy in patients with restored RAI uptake would be without doubt due to the effect of the latter. We decided to investigate not only patients on KI treatment with stable disease but also patients on KI treatment who experience progressive disease. We realize that these patients theoretically have a low chance of having restored RAI uptake. However, no study has investigated whether inhibition growth and RAI uptake could be separate effects of KIs.

The investigation of the effect of the therapy with lenvatinib is another novelty because, to date, few studies have investigated mKIs as re-differentiating agents.

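### Allocation is split by KI type, but the primary chi-square test is pooled and KI type is not in the adjusted model: a conservative test and a modest loss of efficiency

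*Protocol article*

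**What the plan says.** **Allocation.** Section 2.3 gives a 1:1 ratio from an Excel list and states: "The enrolled patients will be divided into groups based on the KI type and then into two subgroups", the two being KI alone and KI plus myo-inositol (MI). The natural reading is randomisation stratified by KI type, although the article does not use that term. Section 2.2 ties KI type to genotype: patients with a BRAF mutation are on selective inhibitors, and those with no mutation or a non-targetable one are on a multikinase inhibitor.

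**Comparison.** Section 2.2 also says that the arms are compared within like KI subgroups.

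**Analysis.** Section 2.3 says: "A chi-square test will be used for the primary endpoint". The sample size is a pooled two-group calculation: "60% in the experimental group and 30% in the control group", and "42 patients per group will be necessary for the effect size indicated above". The adjusted model is described in one sentence: "A multivariate logistic regression will be performed adjusting for gender and age". KI type appears in neither the test nor the model.

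**Factors the article links to uptake.** The Introduction reports restored uptake in 44% of BRAF V600E patients on a MEK inhibitor, and in 1 of 20 patients on the multikinase inhibitor sorafenib. On patients progressing under a KI, the Discussion says: "We realize that these patients theoretically have a low chance of having restored RAI uptake".

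**The concern.** A factor used to balance allocation should normally be carried into the analysis. Balancing on a prognostic factor removes its contribution to the difference between arms. A pooled chi-square test still counts that contribution in its variance, so the test statistic is too small on average. The test then rejects less often than 5% under the null, and some of the precision gained by stratifying is thrown away.

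The article names both the test and the covariates, so the mismatch lies in what it fixes and not in something left to an analysis plan. Section 2.2 adds a second difficulty. It promises comparisons within KI type, while section 2.3 sizes and tests one pooled comparison. If the within-KI comparisons were taken as the primary ones, the 80% power claim would not apply to them.

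**Working it through.** **1. The plan's own sample size.** Inputs from section 2.3: 30% against 60%, alpha 5% (two-sided assumed; the article does not say), power 80%. With mean rate 0.45:

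n = [1.960·√(2·0.45·0.55) + 0.842·√(0.30·0.70 + 0.60·0.40)]² / 0.30² = (1.379 + 0.565)² / 0.09 = 42.0 per group.

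The stated 42 per group, 84 in total, reproduces.

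**2. Assumptions for the check.** The article gives neither the size of the KI groups nor uptake rates for the two regimens studied. I assume 21 patients per KI type in each arm and vary the control rates. All pairs average the article's 30% except 44/5%, which uses the article's cited figures for other drugs (1 of 20 = 5%) and averages 24.5%.

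**3. Why the pooled test is conservative.** With allocation balanced within KI type, the true variance relative to the one the pooled test uses is

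R = mean of p(1−p) over KI types ÷ p̄(1−p̄),

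and the true error is about 2·[1 − Φ(1.960/√R)].

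For 44/16%: R = [(0.2464 + 0.1344)/2] / 0.21 = 0.1904/0.21 = 0.907. The error is about 2·[1 − Φ(2.058)] = 4.0%.

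R cannot exceed 1, so apart from the discreteness of the data the error can only fall.

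**4. Exact enumeration.** Two-sided 5%, 21 + 21 per arm, no continuity correction. Power is for +30 points in each KI type.

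| Control rates | Error: chi-square | Error: CMH | Power: chi-square | Power: CMH | CMH minus chi-square |
|---|---|---|---|---|---|
| 30/30% | 5.1% | 5.1% | 82.8% | 79.7% | −3.0 |
| 40/20% | 4.5% | 5.0% | 83.3% | 82.6% | −0.7 |
| 44/16% | 4.0% | 5.0% | 83.8% | 84.1% | +0.3 |
| 50/10% | 3.0% | 5.1% | 85.1% | 87.6% | +2.5 |
| 44/5% | 2.9% | 5.2% | 85.6% | 88.8% | +3.2 |
| 55/5% (extreme) | 1.9% | 5.2% | 86.7% | 92.0% | +5.3 |

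Differences are taken before rounding. Unequal KI groups behave alike: the chi-square error is 4.0% with 14 + 28 per arm at 50/20%, and 4.0% with 28 + 14 at 40/10%.

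**5. If allocation is not stratified.** With a simple 1:1 split that ignores KI type, simulation (400,000 trials) gives a chi-square error of 5.0–5.1%. The conservatism therefore depends on the stratified reading of section 2.3.

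**6. Separate tests within KI type.** For 30% against 60% at n per arm:

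power = Φ{[0.30·√n − 1.379] / √0.45}.

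At n = 21: Φ[(1.375 − 1.379)/0.671] = Φ(−0.006), or about 50%. It is 35% at 14 per arm and 62% at 28.

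**The case against.** The case for leaving the plan alone is fair in several respects.

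- **Validity.** A reader might infer that the primary test has an inflated error rate. It does not. The error stays at or below about 5%, and it falls only if allocation really is stratified and KI type is prognostic. The article implies the first and does not establish the second for these drugs.
- **Power.** The pooled chi-square exceeds 80% in every scenario in the table. For moderate differences between KI types the CMH gain is nil or slightly negative. At 30/30% CMH falls just below the target.
- **Prognostic strength.** A reader might infer that the strongest known predictors of uptake have been left out. The article ranks no predictors. Its 44% and 1 of 20 come from drugs not used here, and it notes elsewhere that lenvatinib has increased uptake in some studies. Its remark on progressive disease is labelled theoretical. What stands is that the article itself treats both factors as bearing on uptake and gives no reason for preferring gender and age.
- **Disease status in the randomisation.** A reader might conclude that allocation should also be stratified by stable or progressive disease. That is a design preference in a pilot of 84. Chance imbalance on this factor is already covered by the test's error rate.
- **Purpose of the logistic model.** Its sentence follows the one on secondary endpoints, so it may not concern uptake at all. The article should say which endpoint it serves.

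These arguments limit the size of the point. They do not reconcile the like-with-like comparison in section 2.2 with the pooled test in section 2.3.

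**Conclusion.** The point holds as one of efficiency and internal consistency. Allocation is split by KI type and comparison within KI type is promised, yet the stated primary test and the adjusted model both ignore KI type. If allocation is balanced within KI type and KI type predicts uptake, the chi-square is conservative: the error is 4.0% at control rates of 44/16%, and about 3% at 50/10% or 44/5%. At those rates the stratified test adds from nil to about 3 points of power. The group sizes and the rates are assumptions. The documents do not support a claim of excess false positives. The sample size is correct for the pooled comparison and need not change; it does not support separate confirmatory tests within each KI type.

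**What to change.** 1. State in section 2.3 that randomisation is stratified by KI type.
2. Make the primary test a CMH test stratified by KI type on all 84 patients, reported with a common risk difference and its 95% CI. This compares patients on the same KI, as section 2.2 intends, and uses the full sample.
3. Label the separate comparisons within each KI type exploratory.
4. Add KI type to the logistic model alongside age and gender, and say which endpoint the model serves. Disease status at entry (stable or progressive) is an optional further covariate, best named before any data are seen.

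**Cost.** A change of wording. N stays at 84, and KI type is known at entry. The statistical price is about 3 points of power (79.7% against 82.8%) if uptake turns out not to differ by KI type.

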### 2.2. Eligibility Criteria and Study Design

Patients meeting the eligibility criteria described in Supplementary Table S2 will be included. In summary, RAIR-TC patients will need to have had next-generation sequencing (NGS) analysis for possible mutations. Eligible patients will have a BRAF mutation (treated with sKIs), no mutations, or non-targetable mutations (treated with mKIs). Patients must have been taking KIs for at least four months.

All patients will need to give their written informed consent to be included in the study.

The trial’s design is summarized in Figure 1. Patients will be divided into 2 groups: (1) a control group in which patients are treated with KIs (subgroup a: trametinib plus dabrafenib; subgroup b: lenvatinib); (2) a group (divided into the same subgroups), in which patients are treated with the same KIs in addition to MI. Comparisons will be made between the same subgroups.

MI has a half-life of less than 24 h, and a complete steady state can be achieved in about 4–5 days. However, a longer administration (30 days) helps to ensure an effect on the various metabolic activities. After 30 days of MI treatment, all patients, treated with L-T4 at a semi-suppressive dosage as per clinical practice, will be stimulated with recombinant human TSH (rhTSH) (days 31 and 32). On day 35, patients will be subjected to WBS, with hybrid imaging where possible (SPECT/TC), after the administration of diagnostic activity (185–222 MBq) of 123-I in accordance with the SNMMI/EANM guidelines [28]. Blood samples will be collected before starting MI therapy (day 0); after 30 days of MI therapy; and then on days 31, 32, 33, 34, and 35 after MI therapy. The laboratory assessments are reported in Supplementary Table S3. Quality of life (QoL) will be assessed at the beginning of the MI treatment and at the end of its administration.

Patients will be withdrawn from the study if they experience any side effects from the MI or if they experience adverse unmanageable effects from the KIs, although no known side effects of MI have been reported to date.

The study will be terminated early if there is premature evidence of superiority in the MI group. The study will conclude upon evaluation of the primary endpoint.

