### 2.4. Study Aims

The objective of the study is to evaluate the efficacy of 2 g of MI twice a day for RAIR-TC in inducing the re-uptake of RAI in patients during KI therapy. Although evaluating the effectiveness of the chronic treatment of KIs on re-differentiation is not one of the endpoints of the study, some possible speculations are discussed below.

The primary endpoint is the restoration of 123-I uptake in RAIR-TC patients already on KI therapy alone and on KI therapy plus MI. The restoration of 123-I uptake will be evaluated in target lesions. In the case of multiple lesions, only re-uptake in a target lesion will be considered. A regional target/background ratio of more than 4 and a 2-fold higher iodine uptake than the mean uptake in liver parenchyma according to visual assessment will be considered to indicate responders.

The secondary endpoints are (1) the thyroglobulin trend as a secondary marker of differentiation and (2) the safety and QoL of these patients.

Safety will be assessed according to the clinical symptoms and laboratory parameters. This includes the monitoring of adverse events as defined in the Common Terminology Criteria for Adverse Events (CTCAE) v5.0. All the investigators involved in the study will be responsible for reporting all adverse events occurring during the study.

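### Myo-inositol stops on Day 30, five days before the Day 35 scan that supplies the primary endpoint; it should continue through the scan

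*Protocol article*

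**What the plan says.** The schedule is spread over sections 2.2 and 2.3 of the protocol article.

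- **MI dosing.** Section 2.3 has clinical data collected "on the first (Day 1) and last day (Day 30) of the supplementation with MI". Day 30 is therefore the last dosing day.
- **Stimulation and sampling.** Section 2.2 gives recombinant human TSH on Days 31 and 32, once the 30 days of MI are complete. Blood is drawn at Day 0, after 30 days of MI, "and then on days 31, 32, 33, 34, and 35 after MI therapy". Quality of life is assessed "at the beginning of the MI treatment and at the end of its administration".
- **Primary endpoint.** Section 2.2: "On day 35, patients will be subjected to WBS". Section 2.4 describes the endpoint as restored 123-I uptake in patients "already on KI therapy alone and on KI therapy plus MI".
- **Sample size.** Section 2.3 assumes that the difference between arms in "iodine uptake at the end of treatment will equal 30" percent (60% versus 30% as the example). With alpha 5% and power 80% this gives 42 per group, 84 in all.
- **Pharmacology.** Section 2.2: "MI has a half-life of less than 24 h". The Discussion puts it at about 24 h. The reasons given for dosing for 30 days, well beyond the 4 to 5 days needed for steady state, are an effect on metabolic activities (section 2.2) and, in the Discussion, "to enable the optimal incorporation of MI in the plasma membrane".

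Nothing in the text says that MI continues through stimulation or imaging.

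**The concern.** The trial asks whether adding MI to a kinase inhibitor restores iodine uptake, but uptake is measured only after MI has been stopped for five days. The kinase inhibitor is background therapy in both arms. At the scan the arms therefore no longer differ in current treatment, only in past MI exposure.

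The proposed mechanism adds to the concern. The Introduction links MI to TSH signalling through the inositol phosphate pathway, and to retention of the iodide symporter in the membrane. Stimulation with recombinant TSH begins the day after the last MI day.

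Any fading after Day 30 acts on the MI arm alone and pulls the comparison towards no difference. The Discussion presents this as the first study of MI in this role. A null result that cannot tell an inactive supplement from one withdrawn too early would be a poor basis for deciding whether to go on.

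**Working it through.** **1. The plan's own sample size.** Inputs from section 2.3: p1 = 0.60, p2 = 0.30, alpha 5% (taken as two-sided, since that reproduces the stated number), power 80%, 1:1 allocation. Pooled-variance formula without continuity correction, with mean proportion p̄ = 0.45:

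n = [1.960 × √(2 × 0.45 × 0.55) + 0.842 × √(0.60 × 0.40 + 0.30 × 0.70)]² / 0.30²

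= [1.960 × 0.7036 + 0.842 × 0.6708]² / 0.09 = (1.379 + 0.565)² / 0.09 ≈ 42.

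The stated 42 per group is reproduced. Power at 42 is 80.0%, so the number has no slack.

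**2. The interval.** Last MI day 30, scan day 35: 5 days, or 120 h. At a 24 h half-life that is five half-lives.

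**3. Supplement-derived increment remaining.** Fraction left = 0.5^(hours since last dose / half-life). At 24 h:

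| Study day | Event | Hours | Fraction left |
|---|---|---|---|
| 31 | TSH | 24 | 50% |
| 32 | TSH | 48 | 25% |
| 33 | – | 72 | 12.5% |
| 34 | – | 96 | 6% |
| 35 | scan | 120 | 3% |

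Section 2.2 says less than 24 h, so these are upper values. At an assumed half-life of 18 h about 1% is left on Day 35, and at 12 h about 0.1%. The calculation covers the increment from the supplement only. The Introduction notes that the body also makes its own MI, and this does not wash out.

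**4. What fading would do to power.** The article gives no persistence time, so the share of the effect left at the scan is an assumption, shown as a range. Control stays at 30%, the MI arm is 0.30 + 0.30 × share, n = 42 per arm, two-sided 5%, and power is

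Φ{[(p1 − p2) × √42 − 1.960 × √(2p̄(1 − p̄))] / √(p1(1 − p1) + p2(1 − p2))}.

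| Share of 30 points left | MI arm | Power at 42 per arm | n per arm for 80% |
|---|---|---|---|
| 100% | 60% | 80% | 42 |
| 90% | 57% | 71% | 52 |
| 75% | 52.5% | 55% | 74 |
| 50% | 45% | 29% | 163 |

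The 75% row in full: p̄ = 0.4125; numerator 0.225 × 6.481 − 1.960 × 0.6962 = 1.458 − 1.365 = 0.094; denominator √(0.2494 + 0.21) = 0.678; ratio 0.138; Φ(0.138) = 0.555.

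**5. Schedule against wording.** Section 2.3 puts the assumed difference at the end of treatment, which for MI is Day 30. No uptake is measured on Day 30. The only measurement is on Day 35, and section 2.2 itself describes Days 31 to 35 as after MI.

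**The case against.** The case for leaving the schedule alone has several parts.

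- **The endpoint wording may only name the arms.** Section 2.3 uses nearly the same labels for the two groups. This is fair, and the endpoint wording alone would not carry the point. The sample-size statement is harder to set aside, because it names a time.
- **The 30 points may already mean the difference at the Day 35 scan.** On that reading no power is lost relative to plan. This is possible, but section 2.3 ties the figure to the end of treatment and mentions no allowance for a gap.
- **Plasma half-life may be the wrong clock.** The stated aim is membrane loading, and MI is a building block of membrane lipids that TSH signalling draws on. Loading first and stimulating afterwards is coherent, and at the two TSH doses up to 50% and 25% of the increment would still be present. This stands as a reason why the effect may persist, so harm is not proven. It explains a long lead-in, though. It does not explain stopping before the only measurement.
- **The retention shares come from no source.** True. They show sensitivity and are not an estimate.
- **The article is condensed and Figure 1 is not visible.** Also true, but the text in sections 2.2 and 2.3 is consistent about when MI ends.
- **Continuing has a cost.** Section 2.1 requires approval by each centre's ethics committee, so an amendment may have to go to several. Section 2.2 withdraws patients with any MI side effect, and five more days of open-label dosing lengthen the time in which a symptom could be attributed to MI just before the scan. This stands as a cost, though section 2.2 also reports no known side effects of MI.

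**Conclusion.** The concern holds. On the text, MI ends on Day 30 and the primary endpoint is read on Day 35, about five or more half-lives later by the protocol's own figure, with 3% or less of the supplemental increment left.

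Randomisation, the test and the arithmetic behind 42 per group are sound, and a null result would still validly describe a 30-day course followed by a five-day gap. It could not distinguish no effect of MI from an effect that faded. If some fading occurs, the planned 80% power does not hold: it would be 71% with a tenth of the difference lost and 29% with half lost. How much fades is unknown from the document, so confidence in the practical impact is moderate. The change is worth making because continued dosing protects the comparison whether or not the effect persists, and it is cheap.

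**What to change.** In sections 2.2 and 2.3, continue MI at 2 g twice daily in the MI arm from Day 1 through the Day 35 scan, so that dosing covers TSH stimulation, tracer and imaging. Keep quality of life, the blood sample before TSH and the clinical data on Day 30 in both arms, but name them by study day and no longer by the end of MI. Relabel the Day 31 to 35 samples as study days. Scan day, 123-I activity, responder rule, sample size and chi-square test stay as they are.

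**Cost.** Five days × 4 g = 20 g (10 doses) per patient; 42 × 20 g = 840 g for the arm. The daily dose stays at 4 g, the maximum cited in the Discussion. Blood is already drawn on Days 31 to 35, so no visits are added, and no patients are added. An amendment is needed, best made before enrolment, possibly at more than one ethics committee.

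If the sponsor prefers to keep the gap, the article should justify it with a stated persistence time and define the endpoint and the assumed difference as uptake five days after a 30-day course. That would settle the wording but would not remove the ambiguity of a null result.
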